## Abstract

**Background:**

Child stunting (low height-for-age) is a marker of chronic undernutrition and predicts children’s subsequent physical and cognitive development. Around one third of the world’s stunted children live in India. Our study aims to assess the impact, cost-effectiveness, and scalability of a community intervention with a government-proposed community-based worker to improve growth in children under two in rural India.

**Methods:**

The study is a cluster randomised controlled trial in two rural districts of Jharkhand and Odisha (eastern India). The intervention tested involves a community-based worker carrying out two activities: (a) one home visit to all pregnant women in the third trimester, followed by subsequent monthly home visits to all infants aged 0–24 months to support appropriate feeding, infection control, and care-giving; (b) a monthly women’s group meeting using participatory learning and action to catalyse individual and community action for maternal and child health and nutrition. Both intervention and control clusters also receive an intervention to strengthen Village Health Sanitation and Nutrition Committees.

The unit of randomisation is a purposively selected cluster of approximately 1000 population. A total of 120 geographical clusters covering an estimated population of 121,531 were randomised to two trial arms: 60 clusters in the intervention arm receive home visits, group meetings, and support to Village Health Sanitation and Nutrition Committees; 60 clusters in the control arm receive support to Committees only. The study participants are pregnant women identified in the third trimester of pregnancy and their children (n = 2520). Mothers and their children are followed up at seven time points: during pregnancy, within 72 hours of delivery, and at 3, 6, 9, 12 and 18 months after birth. The trial’s primary outcome is children’s mean length-for-age Z scores at 18 months. Secondary outcomes include wasting and underweight at all time points, birth weight, growth velocity, feeding, infection control, and care-giving practices. Additional qualitative and quantitative data are collected for process and economic evaluations.

**Discussion:**

This trial will contribute to evidence on effective strategies to improve children's growth in India.

**Trial registration:**

ISRCTN register 51505201; Clinical Trials Registry of India number 2014/06/004664.

**Electronic supplementary material:**

The online version of this article (doi:10.1186/s12889-015-1655-z) contains supplementary material, which is available to authorized users.

## Background

Undernutrition affects an estimated 165 million children in low and middle-income countries, and contributes to up to 45% of child deaths [1]. Stunting, or low length/height-for-age, is a marker of chronic undernutrition, and predicts subsequent physical and cognitive development [2,3]. Stunted children are more likely to do poorly in school and subsequently have low incomes, contributing to the intergenerational transmission of poverty [3]. The World Health Organisation has called for global action to reduce the proportion of children who are stunted by 40% by 2025 [4], and nutrition is now recognized as central to sustainable development [5].

There is substantial scientific consensus on determinants of maternal and child undernutrition, and emerging agreement on interventions needed to reduce them. These are summarised in Figure 1. Current community strategies to prevent childhood stunting focus on intensifying the coverage of key interventions in pregnancy and the first two years of children’s lives, or the ‘1000 days’ period [6]. At the same time, there is recognition that substantial impact requires preventive action beyond the first 1000 days of life and outwith immediate health and food interventions. Such action should support adequate nutrition in early adolescence, prevent early pregnancies, improve access to clean water and sanitation to reduce environmental gastroenteropathy, support food security, and promote women’s empowerment [7-11]. A key challenge for community interventions in areas with a high burden of stunting therefore lies in seeking impact on its more immediate determinants (infection control, care practices and feeding in the first 1000 days of life), while supporting longer-term changes in more distal determinants.

**Figure 1 Fig1:**
[figure not shown]
Interventions to address maternal and child undernutrition.

Around one third of the world’s stunted children live in India, with the highest prevalence found in the poorest wealth quintiles and among Scheduled Tribe (ST) and Scheduled Caste (SC) communities [12,13]. Around 22% of growth faltering in young Indian children has already happened at birth, and the remainder is largely completed by 24 months [14,15]. The Government of India’s Integrated Child Development Scheme (ICDS) and National Rural Health Mission (NRHM) support many of the direct interventions in Figure 1, but the impact of these programmes has so far been limited: ICDS’ key cadre, the *Anganwadi Sevika*, spends most of her time record-keeping and providing food supplementation to children aged 3–6 years, and comparatively little time promoting growth among children under two [16]. Previous trials of community interventions to reduce undernutrition have either been conducted outside India [17], tested single interventions rather than integrated strategies [18-20], failed to focus on the critical window for growth or, except for one [21], failed to impact on children’s length/height [22-25]. India’s policy advisers have called for urgent efforts to reduce child undernutrition through changes to the ICDS and innovative interventions in 200 high-burden districts [26]. One proposed reform consists of recruiting a second *Anganwadi Sevika* to promote growth in infants and young children [27-29]. There is currently no evidence-based, rigorously evaluated, scalable intervention model for such a worker.

### Study aim

We aim to determine whether a strategy involving a community-based female worker (*Suposhan Karyakarta*, or SPK), modelled on a second *Anganwadi Sevika*, can reduce stunting in children under two by improving feeding, infection control, and care-giving practices.

## Methods

### Setting

The study takes place in two districts: West Singhbhum (Jharkhand) and Kendujhar (Odisha). These districts have a combined population of 3.3 million (>80% living in rural areas), and fewer than half of women are literate [30]. In both districts, over 90% of households have no access to a toilet facility [Ibid.]. The main sources of livelihood in the study areas include rice and millet cultivation, collection and sale of forest products, daily wage labour, and work in brick kilns or mines. Over 40% of community members in the districts are from indigenous communities (*adivasi*). *Adivasi* children have very high undernutrition rates: more than 50% are underweight and stunted, and over 75% are anaemic [31]. Villages in the study districts have a triad of frontline health and nutrition workers: an *Anganwadi Sevika*, who provides supplementary nutrition to pregnant women, breastfeeding mothers and children aged three to six years; an Accredited Social Health Activist (ASHA) who helps community members access essential health services and promotes institutional deliveries; and an Auxiliary Nurse Midwife (ANM), who provides immunisations, essential medicines and antenatal care.

Ekjut (http://www.ekjutindia.org/about-us.html), the civil society organisation leading the study, has been working in West Singhbhum and Kendujhar since 2004, with a focus on improving the health of indigenous communities through participatory approaches [32].

### Trial design

The study is a cluster randomised controlled trial in which 60 clusters are allocated to receive the intervention and 60 clusters act as controls.

### Cluster size and selection

The unit of randomisation is a purposively selected cluster of around 1000 population, consisting of a village and its adjoining hamlets. Clusters are separated by natural boundaries (rivers, hills, or distance) to avoid proximity between intervention and control areas.

### Randomisation

The randomisation, which took place in July 2013, was stratified by district and by number of hamlets per unit (see Figure 2: Trial design). In each district, Ekjut invited village leaders, teachers, frontline workers such as *Anganwadi Sevikas* and ASHAs, members of local governance bodies (Panchayati Raj Institutions), and Women and Child Development functionaries to participate in a meeting. Members of the research team explained the purpose of the study and the randomisation process. A list of numbered clusters was placed on a wall. The list was stratified into three groups: clusters with no hamlets, clusters with one to two hamlets, and clusters with three or more hamlets. Meeting participants placed a set of numbered balls corresponding to the clusters in each stratum in a local ‘tombola’ (lottery device), and sequentially allocated each ball/cluster to the intervention or control arms.

**Figure 2 Fig2:**
[figure not shown]
Trial design.

### Trial participants

Participants are women in the third trimester of pregnancy residing in the study clusters and identified between the 1st of October 2013 and 31st December 2015. Incentivised volunteers report every newly identified pregnancy to a member of the monitoring team. A study monitor then approaches the pregnant woman to explain the study and seek her consent for participation. Every pregnant woman residing in the study clusters and identified between the 1st October 2013 and 10th February 2015 is also asked for permission to follow-up her liveborn child for a period of 18 months. Pregnant women will be enrolled until the 31st December 2015 in order to measure the impact of the interventions on maternal nutrition in pregnancy.

We exclude stillbirths and neonatal deaths, infants whose mothers have died, infants with congenital abnormalities, multiple births, and mother/infant pairs who migrate out of the study area permanently during the study period. We define permanent migration as mother/infant pair missing more than two consecutive interviews (i.e. being absent from the study area for at least six months) at any point during the infant’s 18 months follow-up period.

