### Sample size

The primary outcome of the study is mean length for age Z (LAZ) score at 18 months. In a meta-analysis of complementary feeding trials testing interventions to improve growth, nutrition education interventions had a mean effect size of 0.2 Z scores on LAZ at 18 months (range 0.04, 0.64) [38]. We therefore chose 0.15 as a conservative estimate of the effect size. The intra-cluster correlation (ICC) for stunting was estimated at 0.035 using an analysis of 42 DHS studies and our own data from the study areas [43]. The unit of randomisation (cluster) is a village and its attached hamlets. We expect around 25 live births per year in each cluster. Accounting for 10% attrition due to loss to follow-up and mortality, recruiting all eligible children born over 12 months in 110 clusters (2772 children before and 2520 after attrition), will allow us to detect a difference of 0.15 in mean LAZ scores between intervention and control arms (SD of 1) with 80% power and alpha of 0.05, and a design effect (D) of 1.8, calculated as D = 1 + (25–1) x 0.035. This sample size also gives the trial 80% power to detect a 13% reduction in the prevalence of stunting (from 60% to 52.5%), a 19% reduction in the prevalence of wasting (from 40% to 32.5%), and a reduction in the infant mortality rate greater than 45% (from 100 to 55 per 1000 livebirths) [44]. To account for the possibility of clusters dropping out of the study and for attrition rates exceeding our 10% estimate, we enrolled a total of 120 clusters (villages).

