#### Final analysis

Final analyses will be by intention-to-treat and include all mothers who were pregnant and had a live birth during the recruitment period (1st October 2013 – 10th February 2015) and their infants, regardless of whether they received the intervention or not. We will test for differences between intervention and control areas in the main outcomes of interest using linear regression for continuous outcomes and logistic regression for binary outcomes, adjusting for clustering using random effect models. We will examine levels of missing data for the primary and secondary outcomes, and plan to use multiple imputation if these exceed 10%.

For the final DMC, we plan to carry out three sub-group analyses. The first will examine differences in children’s LAZ at 18 months according to the intensity of their mothers’ exposure to group meetings (number of meetings attended), adjusting for maternal education, multi-dimensional poverty status, and tribal status. The second sub-group analysis will examine differences in growth outcomes between arms by wealth quintile to understand the equity impact of the intervention. The third sub-group analysis will examine differences in growth outcomes for boys and girls. The final analysis will be presented according to the CONSORT requirements for cluster randomised controlled trials [46,47]. Both the interim and final analyses will be conducted by the trial statistician ([name]).

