### Economic evaluation

We will conduct cost and cost-effectiveness analyses to guide policy decisions and inform any subsequent scale up. We will estimate the total and incremental costs of the intervention from a project, provider, household and societal perspective. The project costs of delivering the interventions will be collected prospectively from the project accounts using a standardised data capture tool designed for this purpose in Excel, and converted to economic costs. Costs incurred by health care providers (mainly MTCs in the districts) will be collected using trial monitoring data on the change in service use, combined with key informant interviews and available financial data on the average unit cost of delivering those services. Patient (household) costs will be collected prospectively during follow-up surveys. All costs will be adjusted for inflation using the Indian Consumer Price Index (CPI) and will be presented in Indian Rupees and 2016 International Dollars. Incremental cost-effectiveness will be measured in relation to the *status quo* alternative i.e. doing nothing in addition to the current ongoing activities. Incremental cost-effectiveness ratios (ICERs) will be calculated for the primary outcome measure (i.e. cases of stunting prevented) and selected secondary and summary measures including cases of wasting prevented, cases of infant mortality averted, life-years saved and DALYs averted. Sensitivity analyses will be carried out to assess the robustness of results.

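### The exclusion of neonatal deaths is not limited to the growth outcomes, so it conflicts with the all-live-births analysis and with the infant mortality rate that the plan powers and costs

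*Protocol article*

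**What the plan says.** Four sections of the protocol article bear on which infants are analysed.

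- **Trial participants:** "We exclude stillbirths and neonatal deaths, infants whose mothers have died, infants with congenital abnormalities, multiple births". The same sentence also removes mother–infant pairs who migrate permanently. It names no outcome to which the exclusions are confined.
- **Final analysis:** the intention-to-treat analysis will "include all mothers who were pregnant and had a live birth during the recruitment period", together with their infants. The exclusions are not repeated.
- **Sample size:** after the primary calculation, the article states "This sample size also gives the trial 80% power to detect" effects on stunting and wasting and "a reduction in the infant mortality rate greater than 45% (from 100 to 55 per 1000 livebirths"). Mortality also appears here as a source of attrition: "Accounting for 10% attrition due to loss to follow-up and mortality".
- **Economic evaluation:** incremental cost-effectiveness ratios are planned for several measures, among them "cases of infant mortality averted, life-years saved and DALYs averted".

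Study outcomes refers to Additional file 1 for the secondary outcomes. That file is not shown.

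**The concern.** An infant mortality rate per 1000 live births has all live births as its denominator and includes deaths in the first month in its numerator. A population without neonatal deaths cannot give that rate. It gives the risk of later death among infants who survived the first month, and here the group is narrowed further by removing multiple births and infants whose mothers died, who may well be at higher risk.

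The exclusion also depends on events after allocation. Clusters were randomised in July 2013 and women were identified from 1 October 2013, so every neonatal death in the cohort follows randomisation. The strategy includes a third-trimester visit, visits to infants from birth, and group meetings on maternal and child health, any of which might change newborn survival. If the rule is applied to mortality, such an effect is missing from the deaths averted, the life-years and the DALYs. Those results are meant to inform decisions on scale-up.

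**Working it through.** **1. The conflict in the text.** This step needs no arithmetic.

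| Section | Infants covered |
|---|---|
| Trial participants | Live births minus neonatal deaths, maternal deaths, congenital abnormalities, multiples and permanent migrants |
| Final analysis | All live births in the recruitment period |
| Sample size (mortality) | Rate per 1000 live births |
| Economic evaluation | Infant deaths averted, with life-years and DALYs |

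The first row cannot describe the same infants as the second, and it cannot supply the third or fourth. Excluding stillbirths causes no difficulty, since they are not live births.

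**2. Inputs for the size.** From Sample size: "2772 children before and 2520 after attrition"; a design effect of 1.8 (the formula there gives 1 + 24 × 0.035 = 1.84); "with 80% power and alpha of 0.05". Allocation is 1:1. I assume a two-sided test. The only intra-cluster correlation given is for stunting, so using D = 1.8 for mortality is also an assumption.

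**3. Calibration on the primary outcome.** n per arm = 2(1.96 + 0.842)² / 0.15² = 698 after rounding up. Then 698 × 2 × 1.8 = 2513, against 2520 stated. Power at 2520 is 80.1%, so the primary calculation reproduces.

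**4. Mortality power with neonatal deaths kept.** Power = Φ[(|p₁ − p₂| − 1.96·SE₀)/SE₁], where SE₀ uses the pooled proportion, SE₁ the separate proportions, and n per arm = N/(2D).

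- N = 2520, D = 1.8: n = 700, p₁ = 0.100, p₂ = 0.055, SE₀ = 0.01429, SE₁ = 0.01424. The argument is (0.045 − 0.02801)/0.01424 = 1.193, so power is **88%**.
- N = 2772, D = 1.8: power is **91%**.
- With D = 1.84 the two figures are 88% and 91% (87.7% and 90.5%).

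The stated 80% is lower than these figures. It would correspond to a design effect of 2.27 (N = 2520) to 2.50 (N = 2772).

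**5. Mortality power if the exclusion is applied (illustration).** Let s be the share of infant deaths that are neonatal. The article gives no value, so s = 40–65% is an assumption. The risk among first-month survivors is p₁ = 0.1(1 − s)/(1 − 0.1s). The same 45% relative reduction is assumed, p₂ = 0.55·p₁, and N = 2772(1 − 0.1s). For simplicity the same neonatal loss is taken in both arms, and the other exclusions are ignored.

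| s | p₁ | p₂ | n per arm after D = 1.8 | Power |
|---|---|---|---|---|
| 40% | 0.0625 | 0.0344 | 739 | 71% |
| 50% | 0.0526 | 0.0289 | 732 | 63% |
| 60% | 0.0426 | 0.0234 | 724 | 53% |
| 65% | 0.0374 | 0.0206 | 720 | 48% |

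**The case against.** The best defence is that the exclusions were meant for the growth cohort only. A neonatal death has no length at 18 months, the migration rule is framed around missed follow-up interviews, Sample size gives mortality per 1000 live births, and Final analysis already takes in all live births. Additional file 1 may define mortality with its own denominator. Mortality is also subsidiary: it is absent from the secondary outcomes named in the abstract, from the research questions and from the interim monitoring list.

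Most of this stands as a reading of intent, and it lowers both the severity and the confidence. It does not remove the conflict, because the exclusion is stated without limit and two other sections need the infants that it removes.

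Three stronger readings are not supported:

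- **That the mortality power claim is itself a shortfall.** With neonatal deaths kept, 80% is conservative.
- **That the exclusion prevents any check on differential survival.** Pregnancies are registered, births are followed up within 72 hours, and reporting is to follow CONSORT for cluster trials. Leaving a death out of an analysis does not erase its record.
- **That the mortality results would be biased in a known direction.** This depends on how the intervention affects newborn survival, which is unknown.

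**Conclusion.** The article states an exclusion that contradicts its own intention-to-treat population and cannot yield the infant mortality rate that it powers and costs. That conclusion rests on the visible text alone. This should be fixed. It is not critical, because mortality is not the primary outcome and Additional file 1 may already settle its definition.

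The loss of power, to about 71–48% from the stated 80%, is only an illustration. It depends on the assumed neonatal share, on the same 45% reduction holding after the first month, and on a design effect derived from stunting. The more important consequence is that any newborn-survival effect would be missing from the mortality and cost-effectiveness results if the exclusion were applied to them.

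**What to change.** 1. In Trial participants, state that the exclusions apply only to the anthropometric analyses (LAZ and other growth outcomes).
2. State that infant mortality, and the deaths-averted, life-year and DALY ratios built on it, use all live births to consenting women in the allocated clusters. Neonatal deaths, multiple births and infants whose mothers died are counted.
3. State how infants who migrate are handled in the mortality analysis.
4. In Sample size, state that the mortality power refers to this all-live-births set.
5. Align Final analysis and Additional file 1 with these statements.

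The cost is a change of wording and one further analysis set. Under Data collection, all children born to women recruited in the window are to be followed from within 72 hours of birth, so no new recruitment is needed. The team should confirm that vital status was still recorded for infants dropped under the exclusions. The article describes the trial as still recruiting, so this can be settled before the final analysis.

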### Data collection, cleaning and storage

Across the study area, incentivised volunteers report pregnancies to monitors, each responsible for a population of around 4000. A monitor visits every pregnant woman identified, ascertains the estimated month of pregnancy, offers information about the study and invites her to join. If consent is given, the monitor measure the woman’s height and MUAC, and administers a first questionnaire. All children born to pregnant women recruited between 1st October 2013 and 10th February 2015 will be followed up within 72 hours of birth, and at 3, 6, 9, 12 and 18 months. Trained growth monitors conduct measurements at birth, and then visit the mother and child at 3, 6, 9, 12 and 18 months to measure length (using a Shorr board), weight (using a Seca 384 scale), MUAC, and administer a structured questionnaire. All monitors’ measurements were validated twice against a gold standard, and we calculated intra-observer and inter-observer technical error of measurement for length and other anthropometric outcomes.

We use mobile phones programmed using the CommCare platform for data collection. The monitoring team checks the number of interviews completed and type of data collected every week in order to promptly identify and address possible problems. The data are downloaded every two weeks and checked for errors using automated do files and manual inspections. Names of participants are collected but removed before data storage. Final datasets contain numerical identifiers for cluster individual participants. The data are stored and backed up every two weeks on a server.

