### Study outcomes

The primary outcome of the trial is children’s length-for-age Z scores of 2006 WHO Growth Standards at 18 months. Secondary outcomes are described in Additional file 1, along with details of their inclusion in the interim Data Monitoring Committee (DMC).

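### The missed-interview migration exclusion contradicts the intention-to-treat statement and, as worded, discards returning children who have a measured 18-month LAZ

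*Protocol article*

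**What the plan says.** - **Who is excluded.** The Trial participants section of the protocol article lists several exclusions, among them "mother/infant pairs who migrate out of the study area permanently during the study period". The working definition is "missing more than two consecutive interviews (i.e. being absent from the study area for at least six months) at any point" in the 18-month follow-up. Nothing is said about a pair that comes back.
- **Who is analysed.** The Final analysis section states: "Final analyses will be by intention-to-treat and include all mothers who were pregnant and had a live birth during the recruitment period". It adds their infants, whether or not they received the intervention.
- **Missing data.** The same section says that levels of missing outcome data will be examined and that the authors "plan to use multiple imputation if these exceed 10" per cent. It gives no denominator.
- **Visits and outcome.** Under Data collection, cleaning and storage, children "will be followed up within 72 hours of birth, and at 3, 6, 9, 12 and 18 months". Under Study outcomes: "The primary outcome of the trial is children’s length-for-age Z scores of 2006 WHO Growth Standards at 18 months".
- **Timing.** Under Randomisation: "The randomisation, which took place in July 2013, was stratified by district". Women were identified from October 2013, so every missed interview comes after allocation.
- **Attrition.** The Sample size section treats loss to follow-up, together with mortality, as 10% attrition from recruited children.

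**The concern.** The two sections give incompatible rules for the primary analysis set. One takes every live-born infant from the recruitment window. The other removes infants according to how their follow-up went. An exclusion based on attendance after randomisation gives up the protection of randomisation if attendance differs by arm or is related to growth.

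Three further problems follow from the wording:

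- Because a gap at any time in follow-up is enough, the rule catches children who return and are measured at 18 months.
- The gloss of six months' absence does not match the count of interviews, so two analysts could classify the same child differently.
- If the missing share is worked out after the exclusion, children without the outcome leave the denominator, and the imputation safeguard may not come into play when it should.

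**Working it through.** **1. The plan's own figure.** Inputs from the Sample size section: difference 0.15, SD 1, 80% power, alpha 0.05 (two-sided assumed), design effect 1.8. The standard two-mean formula gives 698 per arm. Then 2 × 698 × 1.8 = 2513, against the stated 2520. With the unrounded design effect, 1 + 24 × 0.035 = 1.84, it is 2569. The target reproduces to within 3%. The 2772 is 2520 × 1.10. The calculation therefore carries loss to follow-up as attrition among recruited children, not as ineligibility.

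**2. Which children the rule removes.** There are six child visits: birth, 3, 6, 9, 12 and 18 months. More than two consecutive misses means a run of at least three.

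| Minimal run missed | First to last missed visit | 18-month visit |
|---|---|---|
| birth, 3, 6 | 6 months | can be attended |
| 3, 6, 9 | 6 months | can be attended |
| 6, 9, 12 | 6 months | can be attended |
| 9, 12, 18 | 9 months | missed |

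Of the 2^6 = 64 attended/missed patterns, 20 contain such a run, and in 8 of those 20 the 18-month visit is attended. This counts patterns and does not estimate how many children follow them. It shows that the wording reaches children with an observed primary outcome.

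**3. The six-month gloss.** Every run of three missed visits spans at least six months, so the count implies the gloss. The converse fails. A child who leaves after the 9-month visit and stays away misses only the 12- and 18-month visits. That is two interviews, hence not excluded by the count, yet the absence is at least 18 − 12 = 6 months.

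**4. The imputation threshold.** Let T be the true share of eligible infants without an 18-month LAZ, and s the share of those who meet the exclusion rule. Neither is in the document. If missingness is computed after the exclusion:

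recorded share = T(1 − s) / (1 − Ts)

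For T = 15% and s = 0.50: 0.075 / 0.925 = 8.1%. Setting the recorded share to 10% gives a trigger point of T = 0.10 / (1 − 0.9s).

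| True T | s = 0.25 | s = 0.50 | s = 0.75 |
|---|---|---|---|
| 10% | 7.7% | 5.3% | 2.7% |
| 15% | 11.7% | 8.1% | 4.2% |
| 20% | 15.8% | 11.1% | 5.9% |
| T above which imputation starts | 12.9% | 18.2% | 30.8% |

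The value s = 0.50 corresponds to losses spread evenly over 18 months: those lost before the 9-month visit (9/18) miss the 9-, 12- and 18-month visits. If returners with a measured outcome are also removed, say 1% to 3% of infants (assumed), the 8.1% becomes 0.075 / 0.915 = 8.2% to 0.075 / 0.895 = 8.4%.

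**5. Effect on the LAZ contrast.** Excluded children without an 18-month length are absent from a complete-case analysis anyway. The rule itself acts only through returners who were measured. Let f be the returners' share of measured children in each arm, and d the amount by which their mean LAZ is lower. Excluding them shifts the intervention-minus-control difference by d × (f_intervention − f_control). With assumed values d = 0.5, f = 1.5% in intervention and 3% in control, the shift is 0.5 × (−0.015) = −0.0075 Z, or 5% of the 0.15 target. With equal f and equal d in both arms it is zero, and it changes sign if the shares are reversed.

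**The case against.** The other side has a good deal to say.

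- *The Final analysis section may be meant to govern.* If so, no child is lost and no denominator shrinks. But nothing in the article says so, and the exclusion text would still have to change.
- *The authors meant families who leave for good.* That is probably the intention. The operative definition, however, rests on missed interviews alone. It does not require that the pair stays away, and it cannot separate migration from refusal.
- *The trigger may not be affected.* This stands. No denominator is given; over all live births, nothing is suppressed. Even after exclusion, a true 15% still triggers imputation if s = 0.25.
- *The child last seen at 9 months is kept by the visit count and counted as missing.* This also stands. That is the right treatment, so the mismatch is an ambiguity, not a further loss of data.

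A reader might infer that the exclusion by itself biases the result materially. For example, losing 10% of control and 5% of intervention infants, with LAZ lower by 0.3 to 0.5, gives (0.05 − 0.10) × 0.3 to 0.5 = −0.015 to −0.025 Z, or 10% to 17% of 0.15. The documents do not support that reading. The rates and the deficit are assumed, and most such infants would have no 18-month length, so their absence is a missing-outcome problem that exists without the rule. In that scenario the error would also understate benefit. The Setting section names wage labour, brick kilns and mines as livelihoods but does not link them to absence or growth, and no section says that worker contact changes who stays.

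**Conclusion.** The point holds as an internal contradiction and a badly worded rule. Three elements need no assumption: the exclusion conflicts with the intention-to-treat statement, it reaches children with a measured 18-month LAZ, and the six-month gloss does not match the visit count.

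The effect on the 10% threshold is conditional on the share being computed after the exclusion. Its size depends on T and s, which the article does not give; 15% recorded as about 8% is an illustration at s = 0.50. The bias in the LAZ contrast cannot be sized from the document. Against a complete-case analysis without the exclusion, it arises only from returners with a measured outcome. The claim that the rule definitely suppresses imputation, or that it shifts the primary result by a known amount, goes beyond the text.

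**What to change.** Reconcile the Trial participants and Final analysis sections before the final analysis:

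1. Remove the migration exclusion from the primary analysis set. Keep it at most as a sensitivity analysis, with the definition stated once, either as a visit count or as a duration.
2. Analyse all otherwise eligible live-born infants in the arm of their mother's cluster of enrolment. Use enrolment and not place of birth, because women enter by residence in a study cluster during pregnancy.
3. Use every 18-month length obtained, whatever the earlier attendance, and treat absence at 18 months as missing data.
4. Compute and report the missing share by arm over all eligible enrolled infants, and apply the 10% rule to that figure. Any imputation should respect clusters and use earlier LAZ. A repeated-measures model would be an alternative, but that is a preference and not needed to cure the contradiction.

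The cost is wording, modest extra analysis work and a slightly higher reported missing rate. No new data are needed. Imputation for children with few earlier lengths will rest heavily on the missing-at-random assumption, which should be stated.
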